**Outcome assessment**

After screening based on the eligibility criteria, participants will be asked to complete a sociodemographic questionnaire including sex, age, education, medical history, drugs, and food supplements (Table 1). To determine the dietary intake of participants to identify energy, and macro- and micronutrient intake relative to migraine, we will use a 3-day food record, assessing two weekdays and one weekend. A well-trained nutritionist blind to the study protocol will instruct participants about how to fill 3-day food records. Food records will be obtained at baseline and after 8 weeks of the intervention. Then, the data will be entered into the Nutritionist IV software to calculate the energy and nutrient intake of the patients. A 24-hour recall will be also used to determine the level of physical activity of the study participants. 

**Migraine assessment **

The migraine headache characteristics including monthly frequency and duration of the attacks will be obtained by a neurologist (FH). Then, patients will be asked to fill questionnaires in terms of frequency and duration of the attacks during the intervention. The severity of pain will be evaluated applying a visual analogue scale (VAS) ranging from 0 to 10. If patients experience no pain, they will instruct to fill 0 and if they suffer from agonizing pain, they will instruct to fill 10 (Zareie et al., 2020 ▶). The Headache Impact Test-6 (HIT-6) scale will also use to assess the degree of disability due to migraine at baseline and at the end of the study. This questionnaire has six questions and examines the effect that migraine has on a person's daily life as a score. In the answer to each question, there are 5 options including never, rarely, sometimes, most often, and always, which have scores of 6, 8, 10, 11, and 13, respectively. The validity and reliability of this questionnaire have been confirmed in a previous study (Ghorbani and Chitsaz, 2011 ▶).

**Assessment of quality of life**

The Migraine-Specific Quality of Life (MSQ) questionnaire will be used to assess the quality of life of migraine patients. The questionnaire consists of 14 questions that assess the quality of life of patients in the last month. The validity of this questionnaire in Iran has been examined by Zandifar et al. (Zandifar et al., 2013 ▶). For each question, a score of one (never) to six (always) is considered, then the sum of the scores of the questions, which is from 14 (minimum total) to 84 (maximum total), will be considered. The sum of the initial scores will be converted to a scale of zero to one hundred, and finally a higher score will indicate a higher quality of life (Zandifar et al., 2013 ▶). To convert the initial score from zero on one hundred scale, we will follow this method: Individual score minus 14 (lowest total score) divided by 70 (distance between the lowest (14) and the highest total score (84)) multiplied by 100. 

**Assessment of mood status (stress, anxiety, and depression)**

A modified DASS-21 questionnaire for Iran will be used to assess mood at the beginning and end of this study (Samani and Joukar, 2007). The DASS-21 subscales consist of 21 questions, seven questions for stress, seven for anxiety, and seven for depression. Each question is scored from zero (does not apply to me at all) to 3 (absolutely applies to me). The subscales should be doubled, then the severity of the symptoms can be determined as shown in Table 2 (Lovibond and Lovibond, 1995 ▶).

**Table 1 T1:** Timeline and applied tests

**Activity**	Time (Week)								
	0	1	2	3	4	5	6	7	8
**Enrollment**	*								
Eligibility screening Informed consent Randomization Allocation	*								
	*								
	*								
	*								
Sociodemographic	*								
Intervention		*	*	*	*	*	*	*	*
Placebo (maltodextrin, 250 mg)		*	*	*	*	*	*	*	*
Intervention (250 mg phytosomal curcumin)		*	*	*	*	*	*	*	*
Compliance and side effects		*	*	*	*	*	*	*	*
Laboratory tests	*								*
VAS	*								*
HIT-6	*								*
MSQ	*								*
DASS-21	*								*
Food record	*								*
Physical activity recall	*								*

**Table 2 T2:** Intensity of each subscale for assessment of mood status

**Severity **	**Depression**	**Anxiety**	**Stress**
**Normal**	0-9	0-7	0-14
**Mild**	10-13	8-9	15-18
**Medium**	14-20	10-14	19-25
**Intense**	21-27	15-19	26-33
**Very intense**	+28	+20	+34

**Assessment of sleep quality **

It was previously shown that episode migraine has an association with migraine (Alstadhaug et al., 2007 ▶; Vgontzas and Pavlović, 2018 ▶), so, we will assess the sleep quality of patients before and after the study using Pittsburg Sleep Quality Index (PSQI) that was previously validated for Iranian population (Farrahi Moghaddam et al., 2012 ▶). The Pittsburgh questionnaire consists of 9 questions that assess bedtime, waking hours, the amount of sleep per day, and other issues related to sleep patterns and mental quality. Each question will be scored between 0 and 3 (0 = not in the past month, 1 shows <1 time in a week, 2 indicates once or twice a week, and 3 shows ≥3 times a week).

**Laboratory assessment**

A well-trained phlebotomist will collect a 10 ml blood sample after 12 hours of fasting from each subject before and after the study. Then, the blood samples will be centrifuged for 10 min at 2500 rpm at room temperature. Enzyme-linked immunosorbent assay (ELISA) will be used to measure the serum levels of serum high-sensitivity C-reactive protein (hs-CRP), Total Antioxidant Capacity (TAC), Total Oxidant Status (TOS), Malondialdehyde (MDA), Superoxide dismutase (SOD), and Nitric Oxide (NO) (KiaZist, Hamedan, Iran). 

**Statistical methods**

The analysis will eventually be performed in the form of Intention-To-Treat (ITT) and Per-Protocol (PP) using the SPSS software, version 22 (SPSS Inc, Chicago, IL, USA). Quantitative data will be reported as mean±standard deviation (SD), and qualitative data will be presented as frequency and percent. Normality of the data will be assessed using Kolmogorov-Smirnov test. Paired t-test will be applied to evaluate the differences in each group before and after intervention. Independent T will be used to show the baseline and endpoint differences between the two groups. We will apply analysis of covariance (ANCOVA) to show differences between two treatment groups after adjusting for confounding variables. P-value less than 0.05 will be considered statistically significant. 

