**Randomization **

Eligible patients who fulfill the inclusion criteria will be enrolled in the study. At first, the included patients will be randomized (1:1) into intervention or control groups. We will use a permutated block randomization approach to stratify subjects according to migraine severity with a block size of 4. We will use a table of random numbers to perform random assignment. In addition, patients will be enrolled and assigned into intervention and control groups by a well-trained nutritionist. Allocation concealment will be performed by sequentially numbered containers. 

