**Power calculation and sample size estimates**

Sample size was calculated using the formula suggested for randomized clinical trials considering the type I error of 5% (α = 0.05) and Type II error of 20% (β = 0.2; power = 80%). Nitric oxide (NO) level was also considered a main outcome, and based on a previous study (Zareie et al., 2020 ▶), sample size was calculated 23 persons for each group. With potential dropout, finally 30 patients will be assigned in each group.

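### Two between-group tests are planned with neither named as decisive, and the ANCOVA names neither the outcome's baseline value nor the severity stratum

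*Protocol article*

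**What the plan says.** Protocol article, Statistical methods, plans three kinds of test, all at P below 0.05:

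- within each group, paired t-tests before and after treatment;
- between groups, t-tests at two time points: "Independent T will be used to show the baseline and endpoint differences between the two groups";
- between groups, an adjusted model: "We will apply analysis of covariance (ANCOVA) to show differences between two treatment groups after adjusting for confounding variables".

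No sentence ranks the endpoint t-test against the ANCOVA, and no covariate is named.

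The Randomization section describes a "permutated block randomization approach to stratify subjects according to migraine severity", so severity is a design factor. Baseline values exist for adjustment. Table 1 marks laboratory tests, VAS, HIT-6, MSQ and DASS-21 at weeks 0 and 8, and the sleep-quality section has the PSQI before and after the study. Under Migraine assessment, a neurologist obtains attack frequency and duration, and patients then report them during the intervention.

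**The concern.** Three things that the section does fix are weak.

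1. **Two between-group analyses without an order of priority.** The endpoint t-test and the ANCOVA can disagree. With both read at 0.05 and neither decisive, the result that is reported can be chosen afterwards.
2. **An unadjusted endpoint comparison.** It leaves out the baseline value and the stratum, both of which are in hand. At stake are precision and, in a trial of 60 patients, protection against a chance imbalance at baseline.
3. **Significance tests at baseline.** Under sound randomisation any baseline difference is due to chance, so these tests answer no question about treatment. Next to an ANCOVA framed around confounding, they create a risk that covariates are chosen from the data.

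**Working it through.** **Inputs from the protocol** (Power calculation and sample size estimates): "type I error of 5% (α = 0.05"; "Type II error of 20% (β = 0.2; power = 80"; nitric oxide as sizing outcome ("Nitric oxide (NO) level was also considered a main outcome"); "sample size was calculated 23 persons for each group".

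**Assumptions, not in the protocol:** two-sided tests; normal outcomes with equal variance; 23 analysed per group; baseline-endpoint correlation r of 0.3, 0.5 or 0.7. Simulations use 40,000 trials per setting.

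**1. The plan's own figure.** The usual formula is n = 2(z₁₋α/₂ + z₁₋β)²/d². No difference or SD is given, so 23 can be neither reproduced nor refuted. Solved backwards, d = (1.960 + 0.842) × √(2/23) = 2.802 × 0.2949 = 0.826. With the t distribution it is 0.845, and with a one-sided normal test 0.733. I use 0.845 below.

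**2. Power if the t-test decides, against baseline ANCOVA.** Adjustment multiplies the variance by 1 − r². The noncentrality is d√(n/2)/√(1 − r²), and d√(n/2) = 0.845 × √11.5 = 2.865.

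| r | 1 − r² | Noncentrality | Power, formula | Power, simulated | n per group for 80% |
|---|---|---|---|---|---|
| none (t-test) | 1 | 2.865 | 80% | 80% | 23 |
| 0.3 | 0.91 | 3.003 | 84% | 83% | 21 |
| 0.5 | 0.75 | 3.308 | 90% | 89% | 18 |
| 0.7 | 0.51 | 4.011 | 98% | 97% | 12 |

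The last column is 23 × (1 − r²), rounded up.

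**3. Two tests without priority.** The last column gives how often the two tests disagree when the back-solved effect is true. The other columns are error rates with no effect.

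| r | Endpoint t-test | Baseline ANCOVA | Win on either | Disagree, effect true |
|---|---|---|---|---|
| 0.3 | 5.0% | 5.0% | 6.4% | 7% |
| 0.5 | 5.0% | 5.0% | 7.2% | 12% |
| 0.7 | 4.8% | 4.9% | 8.0% | 19% |

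Each test alone holds its level. The excess comes only from choosing between them.

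**4. Chance imbalance.** The standard error of a baseline difference is √(2/23) = 0.295 SD. A gap beyond 0.5 SD is 0.5/0.295 = 1.70 standard errors, which occurs in about 9% of trials. A gap D shifts the raw endpoint difference by r × D, so at D = 0.5 the shift is 0.15, 0.25 or 0.35 SD. With no effect, and given a gap beyond 0.5 SD, the endpoint t-test rejects in 8.5%, 14.3% and 25.0% of trials at r = 0.3, 0.5 and 0.7. Baseline ANCOVA rejects in 4.5%, 5.1% and 5.2%.

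**5. Ignoring the stratum.** I assume two equal, balanced strata and a stratum-outcome correlation s. The true variance of the difference is then about 1 − s² of what the t-test estimates, so its error is about 2Φ(−1.96/√(1 − s²)). That gives 4.0%, 2.4% and 0.6% for s = 0.3, 0.5 and 0.7. Simulation with 24 per group gives 3.9%, 2.3% and 0.6%. Adding the stratum to the model restores about 5% and moves power at 0.845 SD from 82% to 85%, 85% to 91% and 89% to 98%.

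**6. Baseline test as a gate.** If ANCOVA were used only when the baseline t-test is significant, power would be 80.5%, 81.1% and 81.5% at r = 0.3, 0.5 and 0.7, so most of the gain is lost. The error rate under that rule is 4.8%, 4.4% and 3.5%. This form of selection costs power and does not add false positives.

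**The case against.** The best defence is that little of this is excluded by the text.

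- **Covariates.** A reader might infer that the ANCOVA adjusts for the wrong variables in place of baseline and stratum. The text does not support that. It lists no covariates, so both may be among them, and a journal article may leave the list to an analysis plan that is not shown. The missing list is therefore not the fault. This stands.
- **Selection from the data.** A reader might infer that the baseline tests will pick the covariates. The section says only that the t-test will show baseline differences. Selection is a risk that the wording leaves open, not a stated procedure. This stands.
- **Week-8 diet and activity.** Both are measured at weeks 0 and 8, but no adjustment for the week-8 values is stated. It should not be read into the plan.
- **Size.** If the ANCOVA already includes baseline and decides, the power gain is already in the plan. The effect of 0.845 SD is back-solved, and the correlations have no source in the protocol. In particular, nothing shows that migraine severity predicts nitric oxide. This stands and makes the figures conditional.
- **Validity.** Over all randomisations the endpoint t-test keeps its level, and ignoring the stratum makes it conservative. This stands too.

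The defence does not reach what the section does state: significance tests at baseline, and an unadjusted endpoint t-test beside an ANCOVA at the same threshold with no priority. A covariate list in an analysis plan would not by itself settle which test decides.

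**Conclusion.** The concern holds in a limited form. The planned analysis is not invalid, but the between-group inference is left open and one of the two candidate tests is the weaker one.

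- Free choice between the tests would put the error rate at about 6.4% to 8.0% in place of 5%, for r from 0.3 to 0.7. This is modest, and it arises only if either result may count.
- If the t-test decides, power of about 4, 10 or 18 percentage points is given up at r = 0.3, 0.5 and 0.7, given 23 per group and 0.845 SD.
- In the roughly 9% of trials with a baseline gap beyond 0.5 SD, the raw endpoint test is materially biased.
- If the stratum is prognostic, ignoring it makes the t-test conservative. That is a loss of precision, not a source of false positives.

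The direction of these effects needs only a non-zero correlation. Their size rests on the assumed values. The change is worth making because it improves the analysis with data that will be collected anyway.

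**What to change.** State one decisive between-group analysis per outcome.

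- **Outcomes measured at weeks 0 and 8:** an ANCOVA of the week-8 value on treatment, the baseline value of that outcome and the migraine-severity stratum, reported as an adjusted difference with a 95% confidence interval.
- **Attack frequency and duration:** the same model with the on-treatment value as response and its own baseline as covariate.
- **Baseline table:** descriptive, without significance tests.
- **Raw endpoint t-test and within-group paired t-tests:** labelled as supportive.
- **Wording:** replace the reference to confounding by the named covariates, fixed before unblinding.

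The cost is a few sentences in the protocol or analysis plan. No new measurement, visit or patient is needed.

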## Discussion

This study is the first clinical trial assessing the effects of phytosomal curcumin on migraine symptoms and complications. Considering the high prevalence of migraine and its several complications, it is indispensable to find novel and safe treatment strategies to reduce pain and migraine attacks, which might result in increased quality of life and improved functional capacity of patients with migraine. Thus, considering the diverse range of beneficial effects of curcumin on different aspects of human health, particularly its promising effects on neurological disorders (Mohseni et al., 2021 ▶), the findings of this trial might be useful in the management of patients in the clinical setting. 

In animal migraine models, nitric oxide concentrations were reported to be reduced in response to curcumin administration, suggesting this reduction is mediated through the antioxidant and antinociceptive effects of curcumin (Bulboacă et al., 2017 ▶; Bulboacă et al., 2019 ▶). Inflammation and oxidative stress play significant roles in the pathogenesis of migraine (Parohan et al., 2019 ▶). Importantly, as previously documented, the antimigraine properties of curcumin might be related to its anti-inflammatory and neuroprotective properties (Mohseni et al., 2021 ▶). Indeed, the antioxidant effects of curcumin are mediated directly through reactive oxygen species (ROS) scavenging and indirectly through induction of the expression of antioxidant/detoxifying enzymes and scavengers including catalase, superoxide dismutase, glutathione peroxidase, and HO-1 *via* a Nrf2-dependent pathway (Tapia et al., 2012). Furthermore, anti-inflammatory properties of curcumin are due to its role in the activation of peroxisome proliferator-activated receptor-γ (PPAR-γ) and inhibition of NF-κB signaling pathway (Jacob et al., 2008). Moreover, curcumin decreases neurotoxicity while increases autophagy and brain-derived neurotrophic factor (BDNF), nerve growth factor (NGF), and glial cell line-derived neurotrophic factor (GDNF). These all cause growth, maturation (differentiation), and maintenance of neurons, and promote survival of these cells (Mohseni et al., 2021 ▶; Borkum, 2018 ▶; Allen et al., 2013 ▶), which might lead to the reduction of migraine pain and other related complications (Figure 2).

Beneficial effects of curcumin phytosomes against a variety of conditions including diabetic microangiopathy and retinopathy, cancer, osteoarthritis, and inflammatory diseases have been documented (Mirzaei et al., 2017 ▶), hence, it seems that in our study it might exert promising effects on migraine patients. 

**Figure 2 F2:**
[figure not shown]
Schematic summary of pathways depicting the possible effects of phytosomal curcumin on migraine and its potential related mechanisms. As shown in the figure, curcumin, as a natural, accessible, safe, and inexpensive phytochemical has some limitations including low bioavailability, instability at physiological pH, and low solubility in water; thus, its combination with phosphatidylserine can effectively reduce the limitations of using curcumin. Phytosomal curcumin might have beneficial effects on migraine attacks and complications through several mechanisms, including reduction in oxidative stress, neuroinflammation, and neurotoxicity. On the other hand, it increases autophagy and brain-derived neurotrophic factor (BDNF), nerve growth factor (NGF), and glial cell line-derived neurotrophic factor (GDNF), which all causes growth, maturation (differentiation), and maintenance of nerve cells (neurons) and promote survival of these cells

Although this study will be the first randomized double-blind clinical trial investigating the effect of phytosomal curcumin on migraine, some limitations such as relatively short duration of the intervention and lack of long-term follow-up should be acknowledged. In addition, considering the ethical issues, the effect of phytosomal curcumin as a monotherapy approach will not be feasible to be assessed.

The protocol for a double-blinded placebo-controlled trial design is described here, in which the effects of phytosomal curcumin supplementation will be assessed on clinical symptoms as well as inflammatory and oxidative stress biomarkers of patients with migraine. It is expected that oral supplementation with 250 mg/day of phytosomal curcumin for 8 weeks will result in relieving migraine signs and symptoms as well as reduction of inflammation and oxidative stress. Findings of the current study will provide evidence-based information in terms of the efficacy of curcumin as a complementary treatment in patients suffering from migraine.
